**Outcomes:**

The primary outcomes will be the prescription of OACs either VKA or NOACs, product codes for OACs are described in (Appendix 2). Status of anticoagulation therapy will be classified as either OAC prescribed or OAC not prescribed. OAC prescription will be defined as the presence of any OACs prescription during the study period. Treatment patterns for OACs users will be evaluated for (1) continuous exposure to OACs: no treatment change until end of follow-up period, defined starting from the date of first prescription to the intended duration of that prescription, plus the duration of any overlapping and successive prescriptions of the same drug within 30 days after the expected end of a prescription. For VKAs, INR measurements if available will be treated as indicator for VKA exposure and therefore treated in the same way as prescriptions; (2) OACs discontinuation: no OACs prescription after a period of therapy without resumption of OACs; (3) OACs switch: this will include four switching categories: from antiplatelet only to OACs, from VKA to NOAC, from NOACs to VKA, and between NOACs switches. OACs not prescribed will be defined as no prescription record of an OACs at any time after NVAf diagnosis, this will also include patients prescribed lone antiplatelet therapy. Proportions of patients prescribed antiplatelets such as aspirin or other antiplatelets (i.e., clopidogrel, ticagrelor, or prasugrel) within the study period will be described for both OACs exposed and not exposed patients. Products codes of antiplatelet agents can be found in (Appendix 2).

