### **Study design**

The first phase of this study will be a large population-based cohort study to identify incident cases of NVAf between January 1st, 2009 and 30th of June 2019; to determine the proportions of NVAf patients who have received a prescription for OACs or no treatment; to examine predictors of OACs prescribing. Given the described study aims and objectives, this study design will allow for a longitudinal analysis of incident NVAf cases and the subsequent timing of OACs prescribing with no comparator groups.

The second phase will be a comparative cohort study that aims to compare the clinical outcomes of NVAf based on their exposure status to anticoagulation therapy. Both patient groups will be identified from phase one and further divided into comparative groups of patients who have been prescribed OACs and patients with no anticoagulation therapy. The comparison will be undertaken after controlling for factors that could influence a patient's exposure to OACs and the outcomes to be explored, more details provided in section M.

Finally, the third phase of this study will be a separate analysis of the treatment group from phase two who have experienced major bleeding events. This study design is suitable for this phase as it will allow for a longitudinal analysis of NVAf patients from the indexed bleeding events and onward to evaluate the clinical outcomes (i.e. stroke, bleeding reoccurrence and mortality) related to OACs resumption or not and the timing of restarting OACs after the bleeding event, it will also allow for post-haemorrhage assessment of stroke and bleeding risk using different risk scores, and the identification of predictors for not resuming anticoagulation therapy.

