## Exposures, outcomes and covariates

### 1. Phase 1 – NVAf Cohort

**Exposures:** At least one diagnostic code of AF which will be defined specifically as a diagnosis of non-valvular AF (as listed in Appendix 1), up to 30th June 2019. Primary care patient clinical, and referral records will be used to identify exposures.

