**Covariates:**

- Patients' demographic information (age, gender, ethnicity, body mass index (BMI), geographic location (rural vs. urban), smoking status, alcohol consumption, Charlson comorbidity index for the severity of comorbidity (Appendix 4), electronic frailty index (eFI), and the index of multiple deprivation (IMD).
- For the sub-group of patients with NVAf and history of cancer, cancer diagnosis will be assessed at the index date of NVAf diagnosis and classified by cancer type into breast, prostate, colorectal, haematological, lung, and other types, and by cancer metastasis status.
- Drugs that affect either stroke or bleeding, or commonly interact with OACs, such as antihypertensive drugs, statins, antiarrhythmics, antidiabetic drugs, anticonvulsants, non-steroidal

anti-inflammatory drugs, corticosteroids, systemic azoles, HIV protease inhibitors and ciclosporin. (Appendix 2).

- The CHA2DS2-VASc stroke risk score that consists of 9 points, one for each of: congestive heart failure (CHF), hypertension (HTN), age  $\geq 75$  years (x 2 points), diabetes mellitus (DM), prior stroke or transient ischemic attack (TIA) or thromboembolism (x 2 points), vascular disease, age 65 to 74 years, and sex category. Information included in the CHA2DS2-VASc score will be identified using Read codes (Appendix 3 and 4), except for age and sex, to build the score and assess the risk of stroke for all included patients in the cohort. Further categorization of eligibility for OACs will be carried according to individual CHA2DS2-VASc scores; “not eligible for OAC” if CHA2DS2-VASc score = 0 in males, or 1 in females; and “OAC eligible” if CHA2DS2-VASc score  $\geq 1$  in males, or  $\geq 2$  in females.

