## **Data/statistical analysis**

1. Phase 1 - NVAF cohort: Annual and crude incidence rates of NVAF cases will be calculated and expressed as person-time at risk with 95% confidence intervals (95% CI). Incidence rates will be calculated by dividing the number of new diagnosed NVAF cases each year by the total population at risk during the same year. NVAF incidence in each calendar year of the study period (2009-2018) will be stratified by age and further standardized by age and deprivation quantiles. Status of anticoagulation therapy will be classified as either OAC prescribed or OAC not prescribed. OAC prescribed patients are those who received prescriptions for OACs during the study period. Treatment patterns for OAC users will be evaluated for OACs continuation, discontinuation or switched). OACs not prescribed will be defined as no prescription record of an OACs at any time after NVAF diagnosis, this will also include patients prescribed lone antiplatelet therapy. Proportions of patients prescribed antiplatelets will be described for both OACs prescribed and not prescribed patients. Baseline demographic, and clinical characteristics, and status of cancer diagnosis across OACs prescribed and not prescribed groups will be presented as number and percentage, mean $\pm$  (SD), or median (interquartile range), as appropriate. For both groups' eligibility for OACs will be described and categorized based on stroke risk according to CHA2DS2-VASc score. Trends in OACs initiation, switching from antiplatelet only to OACs, and from VKA to NOAC will be explored for each year and further stratified by eligibility for OACs and deprivation quantiles. To identify variables independently associated with OACs prescribing multivariate logistic regression models will be used and fitted with the covariates described in section N. Similarly, in a separate analysis for patients with NVAF and previously diagnosed cancer multivariate logistic regression models will be fitted to explore variables independently associated with OACs prescribing (i.e, cancer types and metastasis status). The level of statistical significance was set at  $P < 0.05$ .

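### Phase 1 models ever-versus-never OAC prescription by logistic regression over unequal follow-up, so covariates that mark short survival will look associated with not being prescribed even if prescribing is identical

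*Protocol*

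**What the plan says.** The Phase 1 outcome (Exposures, outcomes and covariates, Phase 1, Outcomes) is binary. On one side, "OAC prescription will be defined as the presence of any OACs prescription during the study period". On the other, "OACs not prescribed will be defined as no prescription record of an OACs at any time after NVAf diagnosis". The Phase 1 paragraph of Data/statistical analysis repeats both definitions.

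The Study design section sets out to "identify incident cases of NVAf between January 1st, 2009 and 30th of June 2019". The Phase 1 exposure definition gives the same closing date.

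The predictor model is stated in Data/statistical analysis: "To identify variables independently associated with OACs prescribing multivariate logistic regression models will be used and fitted with the covariates described in section N". A parallel logistic model is planned for patients with NVAF and cancer. The Phase 1 covariate list includes age, "Charlson comorbidity index for the severity of comorbidity (Appendix 4), electronic frailty index (eFI), and the index of multiple deprivation (IMD"), and classifies the cancer subgroup by type "and by cancer metastasis status". Risk scores are measured at the index date.

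For Phase 1 the visible text gives no ascertainment window, minimum follow-up, follow-up offset, censoring rule or handling of death. Neither follow-up length nor year of diagnosis is a listed covariate. Phase 2, by contrast, uses a one-year window and discusses immortal time.

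**The concern.** Whether a patient is ever prescribed an OAC depends on two things: how readily it is prescribed, and how long the patient is observed. A patient diagnosed in January 2009 who survives has up to 10.5 years in which to count as prescribed. A patient who dies two months after diagnosis has two months. Logistic regression on the ever/never outcome does not separate the two.

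Any covariate that shortens survival therefore lowers the odds of being prescribed mechanically. Adjusting for the other covariates does not remove this, because the effect runs through the covariate's own link with survival. The covariates affected are the ones Specific aim 3 asks about: age, comorbidity, frailty and cancer. The artefact would exaggerate a true under-prescribing association, and would weaken or reverse a true association in the other direction, for example for a comorbidity-based stroke score.

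The same definition pulls down the ever-prescribed proportion among patients diagnosed late in the study period.

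**Working it through.** The protocol states no Phase 1 figure on this point, so there is none to reproduce. The check asks what odds ratio the planned analysis returns when prescribing is identical in both groups and only mortality differs.

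**Inputs from the protocol**
- Entry from 1 January 2009 to 30 June 2019: 10.49 years, taken as T = 10.5.
- At least 120,000 incident cases (Feasibility counts).

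**Assumed inputs (not in the protocol)**
- Uniform entry, and data ending on 30 June 2019.
- Half of patients start OAC at a mean of 0.15 years (rate λ₁ = 1/0.15 = 6.667 per year). Half start at λ₂ = 0.10 per year.
- Mortality μ of 0.08 per year without the factor, and 0.15, 0.20 or 0.40 with it.

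**Formula.** With constant rates and uniform entry over T, the probability of an OAC before death or the end of data is

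P(λ, μ) = λ/(λ+μ) × {1 − [1 − e^(−(λ+μ)T)] / [(λ+μ)T]}.

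**Base case**
- μ = 0.08, early starters: 0.9881 × 0.9859 = 0.9742. Late starters: 0.5556 × [1 − (1 − 0.1511)/1.89] = 0.3060. Mean 0.6401.
- μ = 0.40, early starters: 0.9434 × 0.9865 = 0.9307. Late starters: 0.2000 × [1 − (1 − 0.0052)/5.25] = 0.1621. Mean 0.5464.
- Odds ratio for prescribed: (0.5464/0.4536) / (0.6401/0.3599) = **0.677**. The truth is 1. Simulations with these rates gave 0.67 to 0.68.

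**Range, from the same formula**

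| Late-start rate | Mortality with factor vs without | Prescribed, with vs without | Spurious OR |
|---|---|---|---|
| 0.10/yr | 0.40 vs 0.08 | 0.546 vs 0.640 | 0.677 |
| 0.10/yr | 0.20 vs 0.08 | 0.595 vs 0.640 | 0.825 |
| 0.10/yr | 0.15 vs 0.08 | 0.612 vs 0.640 | 0.885 |
| 0.05/yr | 0.20 vs 0.08 | 0.543 vs 0.575 | 0.881 |
| 0.05/yr | 0.15 vs 0.08 | 0.555 vs 0.575 | 0.923 |

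A separate set of simulations used mortality of 5% versus 15–60% per year. The spurious odds ratio for *not* being prescribed was 1.13 to 1.47 when 60–80% started at diagnosis and the rest at 0.1 per year. It was 1.48 to 4.52 when none started at diagnosis and initiation ran at 0.2 to 1.0 per year. The direction was the same in every scenario.

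**Would a small artefact be declared significant?** Take the weakest row and assume 20% of 120,000 carry the factor. The variance of the log odds ratio is 1/(24,000 × 0.5549 × 0.4451) + 1/(96,000 × 0.5745 × 0.4255) = 0.000211, so the standard error is 0.0145. Then ln(0.923)/0.0145 ≈ −5.5, well past P < 0.05.

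**Late diagnosis.** With μ = 0.08 and no change in practice, averaging λ/(λ+μ) × [1 − e^(−(λ+μ)F)] over the available follow-up F gives about 73% ever prescribed for diagnoses in 2009 (F 9.5–10.5 years), 54% for 2018 (0.5–1.5) and 36% for the first half of 2019 (0–0.5). Under uniform entry, 1/10.5 = 9.5% of cases (about 11,400 of 120,000) have under one year of potential follow-up.

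**Testing two remedies under the base case**
- *Prescribed within 12 months, yes/no, among patients with 12 months of potential follow-up.* P = λ/(λ+μ) × [1 − e^(−(λ+μ))]. This gives (0.9870 + 0.0915)/2 = 0.539 without the factor and (0.9426 + 0.0787)/2 = 0.511 with it, an odds ratio of 0.89. Across the scenarios tried it was 0.80 to 0.98. The remainder comes from patients who die within the year and still count as not prescribed.
- *Time to first OAC, censoring at death and end of data.* In a simulation of 2,000,000 patients the cause-specific rate ratio, stratified by time since diagnosis, was 1.00, while the ever/never odds ratio in the same data was 0.68.

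**The case against.** Four objections have weight.

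- *Model terms.* A reader might infer that survival time and diagnosis date will themselves be reported as predictors. They will not, because neither is a listed Phase 1 covariate. The bias acts only through covariates that mark short survival.
- *Calendar trend.* A reader might infer that the study will show a false fall in prescribing. The protocol does not support that. Data/statistical analysis plans yearly trends in initiation, not ever-prescribed proportions by year of diagnosis. The Study background also cites a steady rise in OAC use over the decade, which works the other way. A downward pull on late diagnoses is established; the net direction is not.
- *Size.* An odds ratio near 0.68 needs a fivefold mortality difference, which may suit metastatic cancer but not age or frailty in general. For milder contrasts the artefact is modest. This stands, and is why a range is given.
- *Importance.* The Study type section calls Phase 1 hypothesis generating. The Phase 2 sections set the comparison groups by a one-year window, so the ever/never definition should not carry into the comparative hazard ratios, although the Technical Summary describes the Phase 2 unexposed by their Phase 1 class. Incidence (aim 1) is unaffected. This lowers the severity.

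In addition, follow-up starting from zero is inferred from the absence of a stated minimum. The study-population definition is very short in the text available and may be cut off, so an entry rule cannot be excluded. A one-year minimum would still leave follow-up of 1 to 10.5 years.

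**Conclusion.** The concern holds in this limited form. As written, the Phase 1 predictor analysis mixes prescribing with length of observation, and covariates that mark short survival will be associated with non-prescription even when prescribing does not differ. This is not detail left for a SAP, since the protocol itself fixes both the outcome definition and the model.

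The direction for mortality-linked covariates is consistent. The size is not known from the protocol: under the assumed rates the spurious odds ratio for being prescribed is about 0.67 to 0.68 for 40% versus 8% annual mortality and about 0.83 to 0.92 for 15–20% versus 8%. It rests on assumed initiation and mortality rates, uniform entry, and data ending on 30 June 2019. The documents do not support the stronger readings: that survival or diagnosis date are reported as predictors, that a false decline over calendar time will be seen, or that Phase 2 is undermined.

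Severity: should be fixed.

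**What to change.** Amend the Phase 1 Outcomes text and the Phase 1 paragraph of Data/statistical analysis.

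- Replace the ever/never logistic model as the main predictor analysis, overall and in the cancer subgroup, with time from NVAF diagnosis to first OAC. Use cause-specific Cox regression, censoring at death, transfer out and end of data, with year of diagnosis as a covariate.
- Report cumulative incidence of first OAC at 12 months with death as a competing event. This will still be lower in high-mortality groups, because fewer of them live to be prescribed. It describes what happened; the hazard ratio carries the predictor question.
- Keep ever-prescribed as a description only.
- Do not rely on a 12-month yes/no outcome alone, because deaths within the year would count as not prescribed.
- State the date on which follow-up ends and any minimum follow-up.

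The cost is a different model on the same data, with results given as hazard ratios and cumulative incidence instead of odds ratios. No new data are needed, and recent diagnoses can stay in because they are censored. The Study design section already intends to look at the timing of prescribing after diagnosis, so the change fits the stated design.

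### The two halves of the Phase 1 primary outcome run on different clocks, so a patient with an OAC only before NVAF diagnosis is both 'prescribed' and 'not prescribed'

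*Protocol*

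**What the plan says.** The Phase 1 Outcomes text (Protocol, 'Exposures, outcomes and covariates') sets up a two-way classification: "Status of anticoagulation therapy will be classified as either OAC prescribed or OAC not prescribed". It then defines each side.

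- Prescribed: "OAC prescription will be defined as the presence of any OACs prescription during the study period".
- Not prescribed: "OACs not prescribed will be defined as no prescription record of an OACs at any time after NVAf diagnosis". Patients on an antiplatelet alone are included here.

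The Phase 1 paragraph of 'Data/statistical analysis' restates both rules with the same anchors: "OAC prescribed patients are those who received prescriptions for OACs during the study period" and "OACs not prescribed will be defined as no prescription record of an OACs at any time after NVAF diagnosis".

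The study period is used as a calendar window. 'Study design' says the cohort will "identify incident cases of NVAf between January 1st, 2009 and 30th of June 2019", and the analysis section refers to "NVAF incidence in each calendar year of the study period (2009-2018", with the closing bracket following.

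'Definition of the study population', as displayed, names only the two data sources. It shows no washout and no exclusion of patients who had an OAC before diagnosis.

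**The concern.** A binary outcome needs categories that are mutually exclusive and exhaustive over one time window. Here one category looks across the whole study calendar and the other looks only forward from diagnosis. An OAC given before NVAF for some other reason satisfies the first rule and leaves the second untouched.

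Three things are at stake in Phase 1.

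- **Proportions.** Aim 2 asks what share of patients received OACs, an antiplatelet alone or nothing. Two analysts following the same text could place the same patient in different groups.
- **Predictors.** The logistic regression relates prescribing status to covariates. Risk scores are taken at each patient's index date, and cancer status at NVAF diagnosis. If a pre-diagnosis prescription can define the outcome, the outcome can come before its predictors.
- **Who is affected.** The background section names earlier major bleeding during anticoagulation as one reason for under-prescription. A patient who bled on an OAC before NVAF and received none afterwards is someone this phase wants to describe as untreated, yet the 'prescribed' sentence would count that patient as treated.

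**Working it through.** No sample size, power or alpha figure depends on this point, so there is no figure of the plan's own to reproduce. The check is to apply both written rules to every possible pattern.

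**Inputs.** Let *pre* mean an OAC prescription inside the study period but before diagnosis. Let *post* mean an OAC prescription after diagnosis, within the study period. From the Phase 1 Outcomes text:

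- prescribed = *pre* or *post*
- not prescribed = no *post*

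| OAC before diagnosis | OAC after diagnosis | Meets 'prescribed' | Meets 'not prescribed' |
|---|---|---|---|
| no | no | no | yes |
| no | yes | yes | no |
| yes | yes | yes | no |
| yes | no | **yes** | **yes** |

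Three patterns are classified once and the fourth is classified twice. Neither section gives a tie-break.

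**Opportunity for overlap by diagnosis date.** The pre-diagnosis part of the window runs from 1 January 2009 to the diagnosis date. It is close to 0 years for a diagnosis in early January 2009 and about 10.5 years for one on 30 June 2019. Later-diagnosed patients therefore have more time in which to acquire a *pre* prescription. This could add an artefact to any comparison of status by year of diagnosis.

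**Reach into Phase 2.**

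- 'Selection of comparison groups/controls' defines treated patients by OAC treatment in the first year after diagnosis, and controls by at least a year without OACs after diagnosis.
- The Phase 2 Exposures text uses the same diagnosis-based windows. A patient with OACs only before diagnosis cannot enter the exposed group under either section.
- The Technical Summary alone picks the Phase 2 comparators by their Phase 1 label. Read that way, some patients could be lost from the comparator pool.

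**After the fix.** With prescribed = *post*, the rows read: not prescribed, prescribed, prescribed, not prescribed. Every pattern falls in exactly one category, the overlap is zero, and no stated figure changes.

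**The case against.** The strongest reply is that this is loose drafting, with no deliberate choice to count pre-diagnosis use. The outcome is described as either/or, the 'not prescribed' clause is explicit about time after diagnosis, and 'Study design' speaks of incident cases and the timing of prescribing that follows. A sensible analyst might code it as intended. That is a fair account of the intent, and it supports the fix. It does not remove the conflict, because the 'prescribed' sentence appears in two sections with the same calendar anchor.

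Four stronger readings are tempting, and the documents do not support them.

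- **That such patients will be counted as prescribed.** Both rules are repeated equally and neither is said to prevail. The text supports ambiguity. Misclassification in that direction follows only if the 'prescribed' sentence is applied.
- **That the Phase 2 comparison is contaminated.** The detailed Phase 2 sections start from diagnosis. Only the Technical Summary relies on the Phase 1 label.
- **That a large share of the untreated group is affected.** The frequency of OAC use only before diagnosis is not given. The expected untreated count in 'Feasibility counts' (12% of 120,000 = 14,400, stated as around 14,000) is also the wrong denominator. That 12% covers at-risk patients with neither OACs nor antiplatelets, whereas 'not prescribed' includes lone antiplatelet users and is not limited to at-risk patients.
- **That prescribing in the cancer subgroup will be overstated.** The background reports higher venous thromboembolism risk in cancer, which makes this plausible. It also stresses higher bleeding risk, and it says nothing about how often such patients took an OAC, stopped before NVAF and never restarted.

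One further caution stands. The population definition is very short as shown, and an exclusion of earlier OAC users in text not displayed would remove the overlap.

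**Conclusion.** Wrong as written, minor to moderate. The two categories of the Phase 1 primary outcome are not mutually exclusive. A patient with an OAC in the study period before NVAF diagnosis and none after it meets both, and under the 'prescribed' sentence use for another reason would pass as treatment of NVAF.

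The consequence is confined mainly to Phase 1, which the protocol itself calls hypothesis-generating: the proportions in aim 2, the regression of predictors, and possibly comparisons by year of diagnosis. Its size cannot be derived from the documents.

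The conclusion rests on two readings: that the study period is a calendar window, as both 'Study design' and the analysis section use it, and that no exclusion of earlier OAC users exists in text not shown.

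**What to change.** In the Phase 1 Outcomes text and in the Phase 1 paragraph of 'Data/statistical analysis', define 'OAC prescribed' as at least one OAC prescription on or after the date of NVAF diagnosis and within follow-up. Word 'OAC not prescribed' as its exact complement over that same window, so that a prescription on the diagnosis date is also handled consistently. If earlier OAC users are in fact excluded, say so in 'Definition of the study population'.

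The cost is one phrase in each of two places. No extra data are needed and no sample size or other stated figure changes. It also brings the definition into line with the prescribing after diagnosis that 'Study design' describes.

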  - Bleeding risk assessment using the HAS-BLED score which consists of 9 points, one for each of: hypertension, abnormal kidney or liver function (1 point each), stroke, history of bleeding or predisposition, labile INR, elderly ( $> 65$  years), and drugs/alcohol concomitantly (1 point each). All information included in the HAS-BLED score will be identified using Read codes (Appendix 3 and 4), except for age, to build the score and assess patients’ risk for bleeding. Labile INR will not be included since it is not recorded consistently in the CPRD and because we aim is to identify the presence of prescriptions for VKA rather than checking for patient’s adherence to VKA. Bleeding tendency or predisposition will be identified through Read codes for anaemia and gastric, duodenal, and peptic ulcers (Appendix 4). Also, since alcohol consumption is not well documented in primary care, whenever possible patients will score a point for this element if there is a Read code record of heavy or problematic drinking. The bleeding risk will be categorized according to HAS-BLED score; low risk (0-1), intermediate risk (2), and high risk ( $\geq 3$ ).
  - Bleeding risk assessment using the HEMORR2HAGES score which consists of the following variables: Hepatic/renal disease (1 point each); ethanol abuse (1 point); malignancy; age  $> 75$  y (1 point); low platelets count (1); re-bleeding risk (2 points); high blood pressure (1); anaemia (1); genetic factors (1 point); falls risk (1 point); stroke (1). All these variables will be identified using Read codes (Appendix 3 and 4), except for age, to build the score and assess patients’ risk for bleeding except for genetic factors which are not accurately captured in the CPRD.
  - Combined assessment of stroke, bleeding, and mortality risk using the GARFIELD-AF model relies on the following variables: age (in years), weight, heart rate, diastolic blood pressure, ethnicity, sex, history of bleeding, heart failure, history of stroke, diabetes, smoking status, dementia, use of antiplatelet, carotid occlusive disease, chronic kidney disease (CKD) (stages III–V) and vascular disease, in which the latter is defined as history of myocardial infarction (MI) or unstable angina, aortic or peripheral artery disease. These conditions will be identified using Read codes (Appendix 3 and 4).
- All risk assessment scores will be measured at each patient’s index date.

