**Outcomes:**

The primary outcomes include the reoccurrence of MB events or CRNMB for patients who did or did not continue OACs, the composite of stroke and other thromboembolic events, bleeding or cardiovascular related mortality, and all-cause mortality. Secondary outcome is the prescription of any OACs after the occurrence of the major bleeding events (VKAs or NOACs). We also aim to explore the timing of reinitiating OACs from the indexed bleeding event until the date of OACs prescription, and whether patients have continued on the same OAC before the index haemorrhage event, were switched to another agent after bleeding have occurred (i.e. from warfarin to any NOACs or from any NOACs to warfarin) or received lone antiplatelet therapy.

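### The INR rule lets a blood test stand in for a VKA prescription without a coverage interval or an exclusion after stopping or after a NOAC start, so VKA and NOAC treatment patterns are measured by different rules

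*Protocol*

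**What the plan says.** All the relevant rules are in the Protocol, under Exposures, outcomes and covariates.

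- **Scope (Phase 1, Outcomes).** "Treatment patterns for OACs users will be evaluated for (1) continuous exposure to OACs", followed by discontinuation as item (2) and switching as item (3).
- **Continuity.** An episode runs from the first prescription over its intended duration and is carried on by overlapping prescriptions and by "successive prescriptions of the same drug within 30 days after the expected end of a prescription".
- **INR.** Still within item (1), and for VKAs only: "INR measurements if available will be treated as indicator for VKA exposure and therefore treated in the same way as prescriptions".
- **Treated or not.** "OAC prescription will be defined as the presence of any OACs prescription during the study period", and "OACs not prescribed will be defined as no prescription record of an OACs at any time after NVAf diagnosis". Neither definition mentions INR.
- **Phase 2, Exposures.** The exposed group must have a continuous VKA or NOAC prescription within one year of diagnosis. Item (1) of Phase 1 is the only place where continuity is defined.
- **Phase 3, Outcomes.** The aim is to "explore the timing of reinitiating OACs from the indexed bleeding event until the date of OACs prescription". INR is neither mentioned nor excluded.
- **HAS-BLED (Phase 1, Covariates).** "Labile INR will not be included since it is not recorded consistently in the CPRD". A second reason given is that the study looks for the presence of VKA prescriptions, not adherence.

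**The concern.** A prescription record says that a drug was issued and for how long. An INR record says only that a test was done. The Protocol gives the second the standing of the first and attaches no conditions. A test may follow the end of VKA treatment or a change to a NOAC, and it may be prompted by bleeding or liver disease. Where that happens, the exposure record is wrong, and the error may be related to the outcomes and to the bleeding-risk covariates.

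Three Phase 1 results are at stake: continuation, discontinuation and switching by drug class. Because Phase 2 borrows the continuity definition and reports hazard ratios by VKA and NOAC (Data/statistical analysis, Phase 2), membership of the VKA-exposed group can be affected as well.

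**Working it through.** The plan gives no figure on this point, so the check is to run the stated rules on the possible cases. Let E be the expected end of the last VKA prescription, let a test be recorded t days later, and let d be the number of days that one INR record covers. The Protocol does not state d.

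**Case 1: VKA stopped, test at t ≤ 30.** Treated as a successive prescription of the same drug, the test falls inside the 30-day window and continues the episode. The episode's end moves from E to E + t + d. With k tests, each at most 30 days after the end of the previous coverage, the end can move by up to k × (30 + d) days.

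- With d = 0: one test adds up to 1 × 30 = 30 days, and two add up to 2 × 30 = 60.
- With d = 30 (an assumption, equal to the permitted gap): one test adds up to 1 × 60 = 60 days, and two add up to 2 × 60 = 120.

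Moving d from 0 to 30 doubles the maximum extension, so two analysts who both follow the text could build different episodes from the same records.

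**Case 2: VKA stopped, test at t > 30.** The test is outside the window and does not continue the episode under item (1). Item (2) has no window: it requires that no OAC prescription follows and that treatment is not resumed. If a test counts as a prescription there too, the discontinuation is cancelled. Nothing in the text prevents this.

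**Case 3: VKA, then NOAC, then a test.** A VKA indicator now follows a NOAC prescription. Under item (3) this reads as a NOAC-to-VKA switch, although no VKA was issued. If the test is also within 30 days of E, it lengthens the VKA episode into NOAC time.

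**Case 4: NOAC stopped, test afterwards.** The INR sentence is confined to VKAs, so the NOAC episode is not lengthened. After the same prescription gap of more than 30 days, a VKA user with tests in the gap may count as continuous, while a NOAC user does not.

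**Case 5: no OAC prescription at any time.** The patient is not an OAC user, so the INR rule does not apply and the patient stays in the not-prescribed group.

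**Case 6: test after an index major bleed.** Phase 3 dates reinitiation by the OAC prescription. A test would count as a restart only if the Phase 1 rule were carried over, and the text does not say that it is.

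Cases 1 to 4 show the defect. Cases 5 and 6 mark its limits.

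**The case against.** The strongest defence is that the rule is already confined. It sits under continuous exposure for OAC users, the episode starts with a prescription, and later records of the same drug must fall within 30 days. An INR therefore cannot open that episode, and a late test cannot prolong it. The rule also has a sensible purpose, which is to recover VKA treatment whose prescriptions are missing from the practice record. The days covered by one test could be left to an exposure algorithm.

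Much of this stands. It disposes of three stronger readings that a reader might infer:

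- **That the rule contradicts the not-prescribed definition,** making a patient with tests alone both exposed and untreated. It does not: prescribed and not-prescribed status both rest on prescriptions.
- **That the rule produces false resumption after a bleed.** Phase 3 has its own prescription-based date. The Protocol also does not say that hospital INR results are captured; the patient-level linkages are HES Admitted Patient Care and ONS death registration.
- **That the Protocol admits INR testing in general is unevenly recorded.** The HAS-BLED remark is about labile INR only.

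The path to the Phase 2 hazard ratios is also narrow. The time-varying exposure described there reclassifies time before OAC initiation, and no censoring at discontinuation is specified, so the stated link is through who qualifies as continuously prescribed.

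The defence does not reach the rest. The 30-day window does not stop a test soon after stopping, or a chain of tests, from lengthening an episode. Items (2) and (3) carry no window. The missing interval is more than detail, because the stated rule equates a test with a record that has a duration.

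**Conclusion.** The concern holds for VKA treatment patterns among patients already classed as OAC users. As stated, the rule can lengthen VKA episodes, cancel discontinuations and create apparent NOAC-to-VKA switches, and it works for one drug class only. It can carry into Phase 2 through the continuity requirement. Case 1 follows directly from item (1). Case 2, and the switch in Case 3, rest on applying the same equivalence in items (2) and (3), which the text leaves open.

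The size is unknown. The document does not say how often INR tests are recorded after a VKA is stopped or in NOAC users, so no percentage bias can be given. The Limitations section does not mention this source of misclassification, and no prescription-only analysis is planned.

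**What to change.** 1. Let an INR record only support continuation of a VKA episode already opened by a VKA prescription, either by bridging two VKA prescriptions or for one fixed interval stated in advance.
2. State that an INR alone cannot start, restart or switch exposure, and does not count after a NOAC prescription.
3. State in Phase 3 that resumption and its date rest on OAC prescriptions only and that the INR rule does not apply.
4. Add a sensitivity analysis of treatment patterns, and of the VKA and NOAC hazard ratios, using prescriptions only.

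The cost is rewording and a change to the exposure algorithm; no new data are needed. The downside is that some VKA users whose prescriptions are issued outside the practice will be recorded as discontinued or not restarted. The document does not give the size of that error either, which is a reason to report both analyses.
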